# Effect of bottled fluoridated water to prevent dental caries in primary teeth: study protocol for a phase 2 parallel-group 3.5-year randomized controlled clinical trial (waterBEST)

**DOI:** 10.1186/s13063-024-08000-4

**Published:** 2024-03-05

**Keywords:** Primary prevention, Community drinking water, Dental caries, Primary prevention, Randomized controlled trial

## Abstract

**Background:**

Fluoridation of public water systems is known as a safe and effective strategy for preventing dental caries based on evidence from non-randomized studies. Yet 110 million Americans do not have access to a fluoridated public water system and many others do not drink tap water. This article describes the study protocol for the first randomized controlled trial (RCT) of fluoridated water that assesses its potential dental caries preventive efficacy when delivered in bottles.

**Methods:**

waterBEST is a phase 2b proof-of-concept, randomized, quadruple-masked, placebo-controlled, parallel-group trial designed to estimate the potential efficacy of fluoridated versus non-fluoridated bottled water to prevent dental caries incidence in the first 4 years of life. Two hundred children living in eastern North Carolina, USA, and aged 2–6 months at screening are being allocated at random in a 1:1 ratio to receive fluoridated (0.7 mg/L F) or non-fluoridated bottled water sourced from two local public water systems. Throughout the 3.5-year intervention, study water is delivered monthly in 5-gallon bottles to each child’s home with instructions to use it whenever the child consumes water as a beverage or in food preparation. Parents are interviewed quarterly to monitor children’s water consumption and health. At annual visits, the presence of dental caries is evaluated with a dental screening examination. Clippings from fingernails and toenails are collected to quantify fluoride content as a biomarker of total fluoride intake. The primary endpoint is the number of primary tooth surfaces decayed, missing, or filled due to dental caries measured by the study dentist near the time of the child’s fourth birthday. Tooth decay is assessed at the threshold of macroscopic enamel loss. For the primary aim, a least-squares, generalized linear model will estimate efficacy and its one-tailed, upper 80% confidence limit.

**Discussion:**

waterBEST is the first evaluation of a randomized intervention of fluoridated drinking water in bottles to prevent dental caries in the primary dentition. This innovative method of delivering fluoridated water has the potential to prevent early childhood caries in a large segment of the US population that currently does not benefit from fluoridated public water.

**Trial registration:**

ClinicalTrials.gov NCT04893681. Registered on March 2022. Last update posted on 10 October 2023. https://clinicaltrials.gov/study/NCT04893681?cond=Dental%20Caries%20in%20Children&term=fluoride&locStr=North%20Carolina,%20USA&country=United%20States&state=North%20Carolina&distance=50&rank=1

## Introduction

### Background and rationale {6a}

Community water fluoridation is the controlled adjustment of fluoride in a public water system to a level that is optimal for preventing dental caries (i.e., tooth decay) while minimizing the risk of dental fluorosis (i.e., enamel hypomineralization). At the recommended concentration of 0.7 mg/L [1], fluoridated water reduces the prevalence and severity of dental caries in both primary and permanent dentitions. In fact, because water fluoridation reduces the excess fraction of dental caries in children in low-income relative to higher-income households [2], it also reduces income-related disparities in the disease.

A 2015 Cochrane review of the public health impact of community water fluoridation synthesized observational studies worldwide that compared a population receiving fluoridated water against a population receiving non-fluoridated water and that evaluated outcomes at least two points in time [3]. It found a caries prevented fraction of 35% in the primary dentition (i.e., deciduous teeth) and of 26% in the permanent dentition. While informative, 71% of the selected studies were conducted before 1975, prior to the widespread use of fluoride toothpaste. To address this gap and to narrow the focus to the US, we merged US county-level estimates of the percentage of the population served by community fluoridated water, obtained from the Centers for Disease Control and Prevention’s (CDC) Water Fluoridation Reporting System, with individual-level dental examination data from National Health and Nutrition Examination Surveys (1999 to 2004 and 2011 to 2014) [4]. Analysis compared dental caries experience in 19,604 children and adolescents who lived either in counties in which ≥ 75% of households were served by fluoridated community water systems or in counties with lower population coverage. We found that even with near-universal use of fluoride toothpaste, dental caries prevented fraction was 30% (95% CL = 11, 48) in the primary dentition, and 12% (95% CL = 1, 23) in the permanent dentition.

As well as being equitable and effective, community water fluoridation is cost-effective. Each year it saves the US an estimated $6.5 billion in averted direct and indirect treatment costs [5]. In fact, the combination of its low implementation costs coupled with its effectiveness at reducing dental caries prompted the Centers for Disease Control and Prevention to name water fluoridation among the ten great public health achievements of the twentieth century [6].

Approximately 200 million Americans, equivalent to 73% of the US population, are served by community water systems containing fluoride at the optimal level [7]. That leaves 110 million Americans, or one in four, unserved by fluoridated community water systems. Many of these water systems will remain unfluoridated because the rapid expansion in population coverage of fluoridated water that characterized the 1980s has now stalled. In fact, in the decade 2008–2018, population coverage increased by less than 1% from 72.4 to 73.0% [8]. Zokaie and Pollick [9] attribute the stalled expansion to the following: political hurdles to implementing a water fluoridation system, unfounded claims of adverse health effects of fluoridated water, and the view that fluoridation is no longer necessary as dental caries has ceased to be a public health problem. The latter is a misperception as a 2019 CDC report showed that dental caries affects the primary teeth of 23% of children aged 2–5 years and the permanent teeth of 37% of adolescents aged 12–19 years [10].

The American public’s growing distrust in the safety of tap water further limits exposure to fluoridated water. Over the period 2013–2018, avoidance of tap water in the US increased from 13 to 20% [11], consistent with greater consumption of bottled water [12]. Virtually all bottled water sold today is unfluoridated, which likely accounts for higher rates of dental caries observed in US children and adolescents who avoid drinking tap water compared to those who drink tap water [13].

So that more of these Americans can access fluoridated drinking water, the waterBEST study is investigating the delivery of fluoridated water in 5-gallon bottles to children living in eastern North Carolina. These children are at elevated risk of dental caries either because many of the water supplies in the region are not fluoridated or because they actively avoid drinking tap water.

Based on the SPIRIT checklist [14], this paper describes the protocol of the waterBEST trial https://waterbeststudy.com/ which is investigating if fluoride in bottled water helps to prevent dental caries in the first 4 years of life.

### Objectives {7}

The primary objective is to estimate the dental caries preventive efficacy of fluoridated bottled water consumption compared to non-fluoridated bottled water consumption in 4-year-olds. Efficacy is defined as the estimated mean difference in the number of decayed, missing, and filled tooth surfaces per child (dmfs) between intervention groups. Its one-sided, upper 80% confidence limit will be calculated to address inferences about plausible efficacy in a future phase 3 trial. The secondary objectives are to describe cohort retention and intervention adherence in each study group, compare safety parameters and total fluoride intake between study groups, and explore potential mediating effects of ingested fluoride from water on the efficacy of the intervention.

The secondary objectives are to:Assess intervention safety and key aspects of intervention adherence.Quantify study participation rate and cohort retention during follow-up.Determine the intervention’s effect on total fluoride intake.Estimate the contribution of ingested water to any preventive effect of fluoridated bottled water on dental caries.

### Trial design {8}

The trial design is a phase 2b proof-of-concept, block randomized, quadruple-masked (participants, investigators, outcomes assessor), placebo-controlled, parallel-group trial evaluating dental caries-preventive effects of fluoridated bottled water compared to non-fluoridated bottled water in young children. Two hundred healthy children aged 2–6-months, along with their parent(s), guardian, or caregiver {hereafter referred to as “parent”}, will be recruited from Lenoir County, North Carolina (NC), or a neighboring county in eastern NC (Wayne, Pitt, Craven Counties). Children will be allocated at random in a 1:1 ratio to receive either fluoridated or non-fluoridated bottled water (Fig. 1).

**Fig. 1 Fig1:**
[figure not shown]
Schematic of the study design

Randomization will be done within each of two strata defined according to the fluoride content of tap water at the child’s primary dwelling: (a) <0.20 mg/L F or (b) ≥ 0.20 mg/L F. The duration of the intervention is 3.5 years.

The schedule of enrolment, interventions, and assessments for the waterBEST study is depicted in Fig. 2.

**Fig. 2 Fig2:**
[figure not shown]
Schedule of enrolment, interventions, and assessments for the waterBEST study. This schedule depicts 42 encounters during the intervention period, representing a child who enrolls at 6 months of age and completes the study on or near their 4th birthday. Total number of encounters can vary from 38 to 48, varying according to age at enrollment and age at study completion

### Methods: participants, interventions, and outcomes

#### Study setting {9}

The study is being conducted in Lenoir Co., NC, USA, and three neighboring eastern NC counties (Wayne, Pitt, Craven). Lenoir Co. was selected as the primary target population because it is the state’s largest city that does not fluoridate its public water system. The initial target for recruitment is children living in Kinston, the largest town and county seat. Kinston has a population exceeding 40,000 in which one third lives below the poverty level. The ~150 children born in the remainder of Lenoir Co. and in three neighboring counties are a secondary target population.

#### Eligibility criteria {10}

See the inclusion and exclusion criteria in Table 1.

**Table 1 Tab1:** Inclusion and exclusion criteria

Inclusion criteria	Exclusion criteria
The child’s primary dwelling is in Lenoir County, NC (the primary target population) or one of three neighboring counties (Wayne, Craven, and Pitt).	Child has a serious illness/es requiring frequent inpatient hospitalization, as reported by the parent at the screening visit.
The child’s parent understands and consents to procedures described in the parental permission and consent form.	Child’s birth weight was less than 1500 g (3 pounds 5 ounces).
Child is aged 2 months to 6 months at the screening visit.	Child’s gestational age was less than 34 weeks.
Child either drinks water (either plain water or water mixed with something) or is expected to drink water by their first birthday, as reported by the parent at the screening visit.	Child uses fluoride supplements, as reported by the parent at the screening visit.
	The child’s primary dwelling at the enrollment visit has tap water that contains > 0.60 mg/L F and the parent/guardian/caregiver expresses a preference that the child drink tap water, not bottled water, for the child’s first 4 years of life. Fluoride concentration of a sample of the dwelling’s tap water is measured at [name] laboratory using the Ion Selective Electrode method. For children who live at more than one dwelling, the primary dwelling is defined as the one at which they usually sleep at least four nights per week.
	Parent states at the screening visit the child will initiate fluoride supplementation before the child’s 4th birthday.
	The parent anticipates that, before the child’s 4th birthday, the child will move to an address more than 30 miles from their address at the time of enrollment.
	The investigators determine that a child living at the same primary dwelling has already been enrolled in the study. (This means that if two or more children fulfilling the inclusion criteria live at the primary dwelling, the parent will be asked to select one such child to be the study participant.)
	Anything that, in the opinion of the principal investigator, would place the participant at increased risk or preclude the participant’s full compliance with or completion of the study.

#### Who will obtain informed consent? {26a}

Trained study personnel obtain informed consent using the *Parental Permission for a Minor Child to Participate in a Research Study* Consent Form. Because children are not legally able to provide consent, federal regulations require that the parents provide permission before children can be enrolled in research. Furthermore, the UNC Institutional Review Board (IRB) has determined that the waterBEST study entails no more than minimal risk, and therefore, the permission of one parent is sufficient. The study personnel explain the research study to the child’s parent, including the annual collection of fingernail and toenail clippings, and answer any questions that may arise to the parent’s satisfaction. They provide sufficient time to decide whether to participate in the trial before obtaining consent. Study staff then ask questions to verify parents’ understanding of the study and record the answers to document the process of informed consent. Once the child’s parent understands and consents to procedures described in the parental permission and consent form, they sign the informed consent document prior to any study-related assessments or procedures.

*Additional consent provisions for collection and use of participant data and biological specimens {26b}*

This research is covered by a Certificate of Confidentiality, which is issued by the National Institutes of Health to safeguard the privacy of research study participants by protecting identifiable research information from forced disclosure.

### Interventions

#### Explanation for the choice of comparators {6b}

The source of the placebo is groundwater obtained from the Black Creek aquifer in Lenoir County, NC, by the North Lenoir Water Corporation, who treat it for public consumption consistent with state and federal requirements for public water systems. It contains a negligible concentration of approximately 0.3 mg/L fluoride.

#### Intervention description {11a}

The study products are drinking water bottled from two public water systems in eastern NC: the New Bern Water Resources Division’s Black Creek aquifer which contains naturally occurring fluoride in a concentration of approximately 0.8 mg/L F and the North Lenoir Water Corporation’s Black Creek aquifer which contains a negligible concentration of fluoride. Both public water systems produce drinking water consistent with state and federal requirements for public water systems [15, 16]. waterBEST study staff collect 600-gallon batches of potable water from each system and transport the batch to the Kinston field center. On the same day, the water is disinfected using ozone sterilization and packaged into 5-gallon bottles using an Ultra 150 bottling system. The Ultra 150 is a fully automated clean-room system that fulfills the requirements of the FDA and FSMA for processing drinking water intended for human consumption.

#### Criteria for discontinuing or modifying allocated interventions {11b}

The PI may discontinue an individual’s intervention if:The enrolled child begins taking fluoride supplements, as reported by the parent during quarterly health checks.The child moves to a primary dwelling where the concentration of fluoride in tap water exceeds 0.60 mg/L F and the parent has expressed a preference that the child drinks tap water.

The PI may withdraw an individual from the study if:A child relocates to a primary dwelling that is more than 30 miles from their address at the time of enrollment.Any adverse event or other medical condition or situation occurs such that continued participation in the study would not be in the best interest of the participant.The participant meets an exclusion criterion (either newly developed or not previously recognized) that precludes further study participation.

#### Strategies to improve adherence to interventions {11c}

Assessment of adherence with intended water use will be quantified using data about water consumption reported by the parent in monthly interviews throughout the 3.5 years of follow-up. In addition, the number of bottles delivered to each dwelling is recorded, along with the number of people at the dwelling who consume study water. Rates of delivery of study water, consumption of study water, and consumption of non-study water during follow-up will each be assessed as measures of intervention adherence.

To promote adherence to the interventions, each dwelling is given a bottom-loading water dispenser that dispenses hot, cold, and room-temperature water at the push of a button. Study staff demonstrate how to load bottles, dispense water, and replace empty bottles as needed, and they give written instructions. Age-appropriate cups, spill-proof bottles, and related drinking aids will also be provided at no cost to study participants. A travel bag is provided to store water and drinking supplies for use when children are away from home.

#### Relevant concomitant care permitted or prohibited during the trial {11d}

All parents are encouraged to clean their child’s teeth using toothpaste. To avoid the risk of ingesting too much toothpaste (e.g., accidentally swallowing half a tube of toothpaste), the parent is given information about fluoride intake, including correct use of toothpaste. Regular dental visits are permitted.

The use of fluoride supplements and use of study water to reconstitute infant formula are not permitted because of the risk of excessive fluoride intake and subsequent dental fluorosis. At quarterly health checks, study staff interview parents and ask questions about the child’s use of fluoride supplements and infant formula. If the child begins taking a fluoride supplement, the intervention is discontinued for the duration of supplement usage. For study children being fed infant formula concentrate, waterBEST provides 3-gallon bottles of non-fluoridated water purchased from Le Bleu Central Distributors of Wilson, NC, with instructions that it be used solely for reconstitution of formula.

#### Provisions for post-trial care {30}

Parents are given a written report of their child’s dental health after the annual dental screening assessment and after the end-of-study dental caries examination. This will include recommendations for dental care, if required.

##### Outcomes {12}

The primary outcome for efficacy evaluation is the dmfs index, a measure of the dental caries experience in the study participant’s primary dentition. It is quantified as the number of primary tooth surfaces (s) that are decayed (d), missing (m), or filled (f). This index is enumerated during a dental examination near the time of the child’s 4th birthday. Efficacy is defined as the estimated difference in adjusted mean dmfs per child between intervention groups, calculated using a least squares general linear model that adjusts for randomization stratum and age in months at the time of the examination. The index of decayed, missing, and filled primary tooth surfaces (dmfs) is the most widely used, validated, and clinically meaningful epidemiological endpoint of dental caries experience in the primary dentition of children in this age range.

There are four secondary outcomes:

Intervention safety is being determined at quarterly health checks by asking parent/guardian about potential adverse events. To determine if differences exist between study groups in rates of adverse events, rates for each study group will be computed as the total number of adverse events (numerator) divided by person-time of follow-up (denominator).

Study participation and cohort retention during follow-up will be enumerated as the number of participants screened, randomized, and completing follow-up data collection. Outcomes will be as follows: proportion of screened participants providing informed consent, proportion of consenting participants randomized, proportion of randomized participants completing follow-up data collection.

Intervention adherence is being determined with questions to parents/guardians at monthly Bottle Consumption Visits about consumption of study water, and consumption of non-study water during follow-up. Intervention adherence will be computed as the usual number of times per day that study water is consumed, either as plain water or when mixed with something. Monthly reports for each study participant will be integrated to create a subject-specific density measure of water consumption by plotting each month’s reported frequency on the vertical axis and the child’s age (in months) on the horizontal axis of a time-series plot for the study participant. The area under the curve of the time series will be calculated using the trapezoid method to represent the study participant’s frequency measure of intervention adherence.

The intervention’s effect on total fluoride intake will be determined from the fluoride content of fingernail and toenail biospecimens, a biomarker of total fluoride intake. Clippings for fingernails and toenails are collected at intervals of 1, 2, and 3 years after randomization. The fluoride content of fingernail and toenail clippings is being measured in mg/kg using a hexamethyldisiloxane-facilitated diffusion assay of nail clippings collected from study participants. The intervention’s impact on total fluoride consumption will be estimated using measurements of mean fluoride content of fingernail biospecimens.

##### Participant timeline {13}

See Figure 3.

**Fig. 3 Fig3:**
[figure not shown]
Participant timeline

##### Sample size {14}

The power calculation for this phase 2b trial is based on the principle that pilot studies should replicate, in miniature, a definitive trial that would be conducted if justified by findings from the pilot study [17]. By definition, such pilot studies lack the statistical power of a definitive trial. Instead, the goal is to calculate the point estimate of the preventive effect size and plausible range of effect size estimates to make the following three decisions:If the pilot study’s point estimate of effect size is zero or less, and there were no significant flaws in the conduct of the pilot study, a definitive trial is contra-indicated (i.e., a null or harmful finding).If the one-tailed, upper 80% confidence limit of the pilot study effect size is less than the a priori threshold of public-health-significance, then a definitive trial is probably unjustifiable because it would require a very large sample size to estimate a meager health benefit.Otherwise, the definitive trial should go ahead using the point estimate from the pilot study as the effect size when calculating the required sample size for the definitive trial.

When applied using estimates of the dmfs index for 3–4 year-olds living in non-fluoridated areas of the US [4], that approach yields a required sample size of 158 subjects (79 per study group), specifying a clinically significant group difference of 1.1 (s.d. = 7.8), equivalent to 37% reduction in mean dmfs, and power of 80%. (Specifically, using the SAS power procedure with options “two sample means ci = diff halfwidth = 1.1, stddev = 7.8,” 1-tailed alpha = 0.2 and probwidth = 0.8.) The required sample size of 158 subjects with 4-year-old dmfs data was increased to 200 randomized subjects to allow for a presumed loss to follow-up of 20% between enrollment and the 4th Birthday Dental Caries Examination.

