### Statistical methods

#### Statistical methods for primary and secondary outcomes {20a}

The statistical analysis for the primary objective will estimate efficacy and the one-tailed, upper 80% confidence limit of the estimate. Efficacy is defined as the estimated difference in adjusted mean dmfs per child between intervention groups, calculated with a general linear model estimated by ordinary least squares using the SAS “GLM” procedure. The dependent variable will be the child’s dmfs index, an integer (count) measure with a potential range of 0–100 surfaces. The main predictor variable will be the study group (modeled as a binary, dummy variable) and covariates will be randomization stratum (modeled as a binary, dummy variable) and child’s age, in months, at the time of the examination (modeled as a continuous variable). An “estimate” statement in the GLM procedure will calculate the adjusted mean and 1-tailed, upper 80% confidence limit.

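### The 80% reported as power for a 1.1 dmfs difference is the probability of reaching a confidence half-width of 1.1; the sample size is right for that goal, the label is not

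*Protocol article*

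**What the plan says.** All the relevant text is in the protocol article, mostly in Sample size {14}.

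- The section introduces a power calculation, then concedes: "By definition, such pilot studies lack the statistical power of a definitive trial". It gives the aim as a point estimate and a plausible range, which feed three rules on whether to run a definitive trial.
- The result of the calculation is a "required sample size of 158 subjects (79 per study group").
- The basis offered for that number is described as "specifying a clinically significant group difference of 1.1 (s.d. = 7.8), equivalent to 37% reduction in mean dmfs, and power of 80" per cent.
- A parenthesis gives the software options: "two sample means ci = diff halfwidth = 1.1, stddev = 7.8", with "1-tailed alpha = 0.2 and probwidth = 0.8".
- The number was "increased to 200 randomized subjects to allow for a presumed loss to follow-up of 20" per cent.
- Statistical methods {20a} matches the estimation aim: "The statistical analysis for the primary objective will estimate efficacy and the one-tailed, upper 80% confidence limit of the estimate". It names no test of zero difference for the primary outcome.

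**The concern.** Two consecutive sentences describe the same 0.8 in different ways. The first calls it power and calls 1.1 a group difference. The second shows a confidence-interval calculation in which 0.8 is a width probability and 1.1 is a half-width. No effect to be detected enters that calculation.

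The distinction matters because stated power is the figure by which a null or small estimate is usually weighed. A reader who does not know the SAS syntax will take away that the trial has 80% power for a 37% reduction. That reader could treat a disappointing estimate as stronger evidence against the intervention than the design can supply.

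**Working it through.** **Inputs.** From Sample size {14}: SD 7.8, half-width 1.1, one-sided alpha 0.20, width probability 0.8, 79 per group, 37% reduction, 20% loss. From Trial design {8}: 1:1 allocation. The calculations use a two-sample t or normal model with a common SD and no gain from covariates.

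**1. Reproduce the protocol's figure as a precision calculation.** The one-sided half-width is t(0.80, 2n−2) × s × √(2/n), where s² is distributed as 7.8² × χ²(2n−2)/(2n−2). Hence

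P(half-width ≤ 1.1) = P(χ²(2n−2) ≤ (2n−2) × 1.1² × n / (2 × t² × 7.8²)).

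| n per group | df | t | χ² bound | Probability |
|---|---|---|---|---|
| 78 | 154 | 0.844 | 167.7 | 0.787 |
| 79 | 156 | 0.844 | 172.1 | 0.821 |

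So 79 is the smallest n reaching 0.8. Conditioning on the interval covering the true difference gives 0.816 at 79 and the same n. A two-sided 80% interval would need 177 per group, so the one-sided precision version is the one used.

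Allowance for loss: 158 / 0.8 = 197.5, which rounds up to 198; the protocol uses 200. This is consistent.

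**2. Try the same inputs as a power calculation.** At one-sided alpha 0.20 and 80% power,

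n = 2 × (0.8416 + 0.8416)² × 7.8² / 1.1² = 284.9, i.e. 285 per group.

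At two-sided 0.20 it is 454 per group. No power calculation tried gives 79.

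**3. Power at 79 per group for a test of zero difference** (a test the protocol does not plan).

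SE = 7.8 × √(2/79) = 1.241, and 1.1 / 1.241 = 0.886.

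- One-sided alpha 0.20: Φ(0.886 − 0.842) = 51.8%; 51.7% by noncentral t.
- Two-sided alpha 0.05: Φ(0.886 − 1.960) = 14.1%; 14.0% by noncentral t.
- Difference detectable with 80% power at one-sided 0.20: (0.8416 + 0.8416) × 1.241 = 2.09 dmfs. The implied control mean is 1.1 / 0.37 = 2.97, so this is a reduction of about 70%.

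**4. Behaviour of the three decision rules.** The section gives its public-health threshold no number, so assume 1.1. The trial leads to a definitive study if the estimate exceeds zero and the upper limit is at least 1.1. The second condition requires an estimate of at least 1.1 − 0.8416 × 1.241 = 1.1 − 1.0445 = 0.0555, which is the stricter of the two. By normal approximation:

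- True difference 1.1: P(proceed) = 1 − Φ((0.0555 − 1.1)/1.241) = 1 − Φ(−0.8416) = 80%.
- True difference 0: P(proceed) = 1 − Φ(0.0555/1.241) = 1 − Φ(0.0447) = 48%.

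**The case against.** The strongest defence has three parts.

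**The method is disclosed and the aim is estimation.** The options appear in the very next sentence, and the section and the statistical methods both frame the primary aim as an estimate with a one-sided limit. The concession about power is relative to a definitive trial, so it does not flatly contradict an 80% figure. All of this stands. It limits the fault to a wrong label on a correct calculation, but the label is still wrong.

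**The 52% belongs to a test nobody plans.** This also stands. A reader might infer that the trial's real power is 52%. The documents do not support that as a property of the planned analysis: there is no primary test of zero difference, and the figure depends on the alpha chosen (52% at one-sided 0.20, 14% at two-sided 0.05). It is useful only to show that 80% is not power in the usual sense. Nor do the documents support reading this as an arithmetic error or an undersized trial, since 79 per group reproduces exactly.

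**Under the decision rules, 80% has a meaning.** With 1.1 as the threshold, a true difference of 1.1 leads to proceeding 80% of the time. This too is related to n. By normal approximation with known SD, below about 72 per group (2 × (7.8 × 0.8416/1.1)² = 71.2) the zero-estimate rule becomes the stricter one and the probability falls under 80%. Above that it stays at 80% however large n becomes, because it is simply the coverage of the limit. So it weakens the claim that a true effect of 1.1 would often be wrongly abandoned: that risk is about 20%. It does not make the reported figure power, and the section does not offer this explanation.

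**Conclusion.** The point holds as a mislabelled operating characteristic. The 80% is a width probability (achieved value 0.82 at 79 per group), and 1.1 entered the calculation as a half-width. The sample size of 158, raised to 200, is right for that purpose. The design does not have 80% power for 1.1 dmfs in the usual sense, which would need about 285 per group at one-sided alpha 0.20.

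The consequence is moderate. No analysis or sample size changes, and if 1.1 is the threshold, the chance of stopping wrongly at a true 1.1 is about 20%. The larger weakness left unstated is the roughly 48% chance of proceeding when there is no effect.

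The precision and power figures rest on SD 7.8, 79 evaluable children per group and no covariate gain. The decision-rule figures also rest on the assumed threshold of 1.1.

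**What to change.** Keep 158 evaluable and 200 randomized. In Sample size {14}:

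1. Replace the power and group-difference wording with a precision statement, for example: *79 children per group give at least 80% probability that the half-width of the one-sided 80% confidence interval for the difference in mean dmfs is no larger than 1.1, assuming an SD of 7.8.*
2. Either drop the word power, or give it with its conditions: about 52% at one-sided alpha 0.20 and 14% at two-sided 0.05, for a true difference of 1.1 with 79 per group, noting that no such test is planned.
3. Preferably, state the numerical threshold used in the second decision rule and report the probability of proceeding under the three rules. With a threshold of 1.1 these are about 80% at a true difference of 1.1 and about 48% at zero.

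The cost is wording only, though the figures stated will look less favourable.
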